##### Microbiome analysis

The saliva, urine, and fecal samples collected will be analyzed to examine microbiota diversity, richness, and taxonomic composition (65). First, the genomic DNA will be extracted from homogenized fecal samples using the QIAamp Fast DNA Stool Mini Kit (Qiagen, GmbH, Hilden, Germany), following the manufacturer's instruction (65). Then, the polymerase chain reaction (PCR) amplification of the V3-V4 region of 16S rRNA genes with primers Bakt_341F(CCTACGGGNGGCWGCAG) and Bakt_805R (GACTACHVGGGTATCTAATCC) (84) will be performed as the following protocol: 3 min at 95 °C, 25 cycles of 30 s at 95 °C, 30 s at 55 °C, and 30 s at 72 °C (65). Taq DNA polymerase used is the Phusion^®^ High-Fidelity DNA polymerase (M0530S, New England Biolabs, USA). Sequencing libraries will be generated using NEBNext^®^ Ultra DNA Library Prep Kit for Illumina (New England Biolabs, USA). Amplicons will be sequenced using 2 × 250 base pair (bp) paired-end protocol by Illumina HiSeq 2500. USEARCH (version 1.9) (85) will be used to quality filter, cluster, and remove chimeras from demultiplexed 16S rRNA raw sequencing data of the samples. The clustered sequences at 97% similarity level will be utilized to construct operational taxonomic units (OTU) tables and representative sequences will be assigned taxonomy from phylum to species based on the Ribosomal Database Project (RDP) 16S rRNA training set (Version 16) (86).

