### Statistical analysis

The IBM SPSS Statistics software version 27 (IBM Corp., Armonk, NY, USA) will be used to analyze the data. Categorical variables will be presented in frequency and percentage, while continuous variables are presented as mean ± standard deviation (SD). The normality of continuous data will be tested using the skewness test (89). Gut microbiota will be analyzed in terms of alpha diversity, beta diversity, and differential abundance of OTUs (87). The incidence rates of asthma, eczema and gastrointestinal disorders among infants will also be calculated. Principal coordinate analysis (PCoA) plots with phylogenetic and non-phylogenetic distances will be plotted (87). One-way ANOVA with corrections (Bonferroni method) and Tukey HSD test will be carried out (89) to test for statistically significant differences in taxonomic richness, diversity measures, bacterial load, and bacterial abundances. Permutational multivariate analysis of variance (PERMANOVA) based on Bray–Curtis distances and 1,000 permutations (89) will be used to evaluate which factors are associated with the composition of the microbiota.

A generalized linear model (GLM) will be used (90) to determine the associations between predictors and gut microbiota and the association between gut microbiota and infant health after controlling for confounders. The strength and precision of each association will be determined using the relative risk (RR) with 95% confidence intervals (CI) after adjusting for potential confounders. The significance level for all statistical analyses will be set at *p* < 0.05. Meanwhile, the Bonferroni correction will be applied to counteract the effect of multiple testing and avoid multiple spurious positives (91). The alpha value will be adjusted to account for the number of comparisons performed (91).

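### One-way ANOVA/Tukey is the only test named for bacterial abundances. It is poorly calibrated for sparse, skewed taxa: too liberal in strongly unequal groups, conservative in equal ones.

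*Protocol article*

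**What the plan says.** Under Statistical analysis, the protocol article plans to study gut microbiota by "alpha diversity, beta diversity, and differential abundance of OTUs". The test follows two sentences later: "One-way ANOVA with corrections (Bonferroni method) and Tukey HSD test will be carried out", applied to "differences in taxonomic richness, diversity measures, bacterial load, and bacterial abundances". No other test is named for abundances.

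The same section plans a skewness test of normality, summarises continuous variables as mean and SD, uses PERMANOVA for overall composition, and uses a GLM (family and link not given) for confounder-adjusted associations. On multiplicity it adds a Bonferroni correction: "The alpha value will be adjusted to account for the number of comparisons performed".

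Under Microbiome analysis, the data source is V3-V4 amplicon sequencing: "The clustered sequences at 97% similarity level will be utilized to construct operational taxonomic units (OTU) tables", with taxonomy assigned from phylum to species. No quantitative assay of total bacteria is described there.

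**The concern.** OTU abundances usually contain many zeros and a few very large values, and they are relative: a rise in one taxon lowers the others. ANOVA and Tukey HSD rely on roughly normal group means with similar variances. That holds well enough for many alpha-diversity indices, but not for a taxon found in a minority of infants.

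The mechanism is simple with two groups, where ANOVA is the pooled t-test. With 10 against 150, one large value in the small group moves that group's mean by a tenth of its size, while the pooled variance is set mainly by the other 150 infants. A single infant can then produce a very small p-value. The damage sits in the far tail, which is where a Bonferroni threshold operates, so the correction does not give the protection it is meant to give. With equal groups a large value inflates the variance as much as the mean difference, and the test rejects too rarely.

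The third and fourth objectives (factors associated with the infant microbiota, and the microbiota's association with infant health, both at 12 months) depend in part on taxon-level results.

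**Working it through.** **1. The plan's own sample size, to fix the number of completers.** Inputs from Participant selection: effect size 0.427 (read as Cohen's d, two equal groups), two-sided 5%, power 80%, attrition 29.0%.

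- n per group = 2 × (1.960 + 0.842)² / 0.427² = 86.1, so 87; total 174.
- 174 × 1.29 = 224.5, so 225. The stated figure is reproduced.
- Completers: 225 × 0.71 = 159.75, about 160.

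**2. Group sizes implied by the Introduction's prevalences.**

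- Wheeze 6.1%: 160 × 0.061 = 9.8, about 10 against 150.
- Regurgitation 10.5%: 160 × 0.105 = 16.8, about 17 against 143.
- Eczema 27.6%: 160 × 0.276 = 44.2, about 44 against 116.
- Equal groups, for reference: 80 against 80.

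**3. Null rejection.** The test is t = (mean₁ − mean₂) / √[s²pooled (1/n₁ + 1/n₂)] on 158 df. One-way ANOVA and Tukey HSD are identical to it for two groups. Each taxon has the same distribution in both groups: zero with probability 1 − prevalence, otherwise lognormal. The level is 0.05/500 = 0.0001. The 500 OTUs, the prevalence and the log-SD are assumptions. Each cell uses 200,000 simulated taxa and shows the rejection rate divided by 0.0001.

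| Taxon | 10 v 150 | 17 v 143 | 44 v 116 | 80 v 80 |
|---|---|---|---|---|
| Present in 100%, log-SD 1 | 26 | 10 | 0.7 | 0.2 |
| Present in 100%, log-SD 2 | 78 | 19 | 0.7 | 0.0 |
| Present in 30%, log-SD 1 | 36 | 13 | 1.4 | 0.1 |
| Present in 30%, log-SD 2 | 91 | 22 | 0.5 | 0.0 |
| Normal data | 1.1 | 0.9 | 0.8 | 1.1 |

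Only about 20 rejections are expected per cell at nominal, so values near 1 are imprecise. The normal row shows that imbalance alone is harmless; it takes skew and imbalance together. At an unadjusted 0.05 the 10 against 150 rates are only 5.1 to 6.8%, so the problem is confined to the small thresholds that the multiplicity correction creates. At 80 against 80 and a nominal 1%, the 30%, log-SD 2 taxon is rejected 0.1% of the time.

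**4. Does a simple change help?** At 10 against 150 and level 0.0005 (100 OTUs):

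- A log(x + 1) transform before ANOVA leaves 2 to 28 times nominal, over taxa from fully prevalent to 5% prevalence.
- A rank test with normal approximation gives 0.4 to 5.0 times, against 11 to 53 for raw ANOVA on the same taxa. The 5.0 is for a taxon present in 10% of infants, so the sparsest taxa still need exact or permutation p-values.

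**5. Power lost to the test itself.** Bonferroni is kept throughout, with 500 lognormal taxa (log-SD 1.5) and 10% of them shifted by d on the log scale.

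| | Raw ANOVA | Rank test |
|---|---|---|
| 80 v 80, d = 0.427 | 0.5% | 9.2% |
| 80 v 80, d = 0.6 | 1.8% | 38% |
| 44 v 116, d = 0.427 | 2.4% | 4.7% |
| 44 v 116, d = 0.6 | 8.5% | 24% |

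**6. Power lost to Bonferroni, shown separately.** Normal data, 44 against 116, 500 OTUs, 10% truly different. The noncentrality is d√(44 × 116/160) = 5.648d, and the critical t at 0.0001 is about 3.99.

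- d = 0.6: Bonferroni 28%, Benjamini-Hochberg 66%.
- d = 0.427: Bonferroni 6%, Benjamini-Hochberg 18%.

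The realised false discovery rate was about 4% in both.

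**The case against.** The strongest reply is that the article never says which groups the ANOVA compares. They might be feeding pattern, delivery mode or ethnicity, with moderate imbalance, where step 3 shows no inflation. Adjusted associations with infant health are assigned to a GLM, so a reader who infers that wheeze will be tested by ANOVA at 10 against 150 goes beyond the text. In addition, 6.1% is a wheeze prevalence from another cohort, while the planned asthma instrument is the Asthma Predictive Index. All of this stands, and it is why the false-positive figures are conditional.

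Three other strong readings also lack support:

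- **Any unequal split inflates error.** The article's own eczema split does not.
- **Bonferroni is a mistake.** The article states the aim of avoiding spurious positives, and family-wise control serves it. Choosing FDR is partly preference. At the protocol's effect size of 0.427, FDR still misses most true taxa, so sample size is the larger limit.
- **The trial will report a particular number of false OTUs.** That would require every OTU to share one assumed distribution.

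It is also fair that a condensed article may leave the consequence of the skewness test, and any filter, to the full protocol. But naming ANOVA/Tukey for abundances is a choice the article makes, not a detail it leaves out. The link between the OTU analysis and the ANOVA sentence is inferred, though no other test for abundances is offered.

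**Conclusion.** The point holds as one of test choice. Raw one-way ANOVA/Tukey is the only test named for bacterial abundances, and it is poorly calibrated for sparse, skewed taxa. In strongly unequal groups it rejects null taxa about 25 to 90 times (10 against 150) or 10 to 22 times (17 against 143) the Bonferroni level of 0.0001. At 44 against 116 it is close to nominal. With equal groups it is conservative and loses much of the power a rank test would have.

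The sizes rest on 160 completers, 500 OTUs, taxon prevalence of 30 to 100% and log-SD 1 to 2. Only the first follows from the document. Whether the inflation occurs in this study depends on ANOVA groups that are not stated.

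Bacterial load is a side point. The sequencing described yields relative counts, but a quantitative assay may be specified in the full protocol, so the article does not show that the endpoint cannot be measured.

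**What to change.** - Keep one-way ANOVA/Tukey for alpha-diversity indices that are roughly normal, and say which groups are compared.
- For taxon abundances, state a prevalence filter (for example, present in at least 10% of infants) and replace raw ANOVA/Tukey with a rank or permutation test, or with a compositional method (a model on CLR-transformed abundances, or ANCOM-BC). Where groups are small and taxa sparse, use exact or permutation p-values with the rank test.
- Optionally, use Benjamini-Hochberg at 5% for the taxon screen in place of Bonferroni, decided before results are seen.
- Report bacterial load only if a quantitative assay is part of the full protocol, and name it.

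The cost is analysis wording and free software alongside SPSS, with no new data. The price is that effects are reported on a rank or log-ratio scale and, if FDR is adopted, that control is of the false discovery rate rather than the family-wise error. The compositional options were not simulated here; only the rank test was.

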Research on gut microbiota and the key determinants of microbial variation among Southeast Asian children remains lacking (52). Specifically, the Malaysian Working Group on Gastrointestinal Health reported a lack of research and awareness on the role of gut microbiota in early life (53). Increased awareness on the importance of gut health will help establish pre-natal and post-natal factors that promote healthy development and functioning of the immune system, gastrointestinal health, and metabolism in infants. In Malaysia, previous studies on gut microbiota mainly focused on pre-adolescent (52, 54) and pre-school children (55). While there are few local mother-infant cohort studies (45, 56, 57), none observed changes in infant gut microbiota over time.

Overall, it is essential to understand the host-microbe interactions in the first year of life since this period is crucial for infant health programming and may influence infant development with short- and long-term health consequences (1–3). The lack of evidence, especially from the Southeast Asia, calls for further studies to understand how gut microbiota in early life affects disease development (allergy, eczema, metabolic disease, and gastrointestinal disease) into adulthood. Since there is a lack of longitudinal research on infant gut microbiota in Malaysia, this cohort study aims to determine the association between gut microbiota with infant health (temperament, gastrointestinal disorders, eczema, asthma, and developmental delays) during the first year of life at different follow-ups. The specific objectives include:

To assess infant gut microbiota (composition, taxonomy, diversity, and abundance) during the first year of life.To assess temperament, gastrointestinal disorders, eczema (presence and severity), asthma (likelihood of developing), and developmental delays of infants.To determine the associations between socio-demographic, pre-natal and post-natal factors with gut microbiota in infants at 12 months.To determine the associations between infant gut microbiota and infant health (temperament, gastrointestinal disorders, eczema, asthma, and developmental delays) at 12 months.

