### Data collection timeline

Data collection will be conducted from June 2022 to December 2024. Once the recruitment of participants begins, pregnant mothers in their first trimester will be given an information sheet explaining the purpose of the study, and those who agree to join the study are required to provide written informed consent. Data will be collected from the eligible pregnant women during their first trimester (8–12 weeks), second trimester (24 weeks), third trimester (34 weeks) and follow-up infants and mothers post-natally after birth (1–5 days after delivery), at 10–15 days, 1 month, 4 months, 6 months and 12 months of age with a total of nine follow-ups to collect mother-infant biological samples and other relevant information for the research. Types of data and samples to be collected from mothers and infants at each time point are summarized in Figure 1.

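### 1,000 PERMANOVA permutations cannot support the planned Bonferroni correction beyond 50 tests, and give fragile results from 26 tests on

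*Protocol article*

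**What the plan says.** All the governing statements stand in the Statistical analysis section of the protocol article.

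- The permutation count is a fixed number: PERMANOVA on Bray–Curtis "distances and 1,000 permutations (89) will be used to evaluate which factors are associated with the composition of the microbiota".
- The level is common to everything: "The significance level for all statistical analyses will be set at *p* < 0.05".
- Multiplicity is handled by one method: "the Bonferroni correction will be applied to counteract the effect of multiple testing and avoid multiple spurious positives". The divisor follows the analysis: "The alpha value will be adjusted to account for the number of comparisons performed".

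PERMANOVA is not exempted from the correction. The section does not say how many PERMANOVA tests there will be or which tests form a family, and it does not let the permutation count rise as the adjusted level falls.

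The related aim is objective 3 in the Introduction: "To determine the associations between socio-demographic, pre-natal and post-natal factors with gut microbiota in infants at 12 months".

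**The concern.** A permutation p-value has a floor set by the number of permutations. A Bonferroni threshold falls as tests are added. Here the floor is fixed in advance and the threshold is left to float, so beyond some number of tests the two cannot meet. A strong determinant of community composition would then be reported as not significant because of a software setting, and nothing in the output would show why. PERMANOVA is the only test that the section names for whole-community composition. Short of that point, the verdict on a real factor can turn on one or two random permutations.

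**Working it through.** The article gives no minimum p-value, test count or adjusted level, so there is no stated figure to reproduce.

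**Inputs**

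- Permutations: B = 1,000 (Statistical analysis).
- Overall level: 0.05, strict inequality (same section).
- Number of tests m: not stated, so it is varied below.
- Infant ages: six, namely 1–5 days after delivery and then "at 10–15 days, 1 month, 4 months, 6 months and 12 months of age with a total of nine follow-ups" (Data collection timeline; the nine include three antenatal visits). That infant stool is collected at all six is an assumption. It fits the text on sample collection, where kits are handed out at each visit, but Figure 1 is not shown.

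**1. Floor of the p-value.** With b exceedances among B random permutations, the valid p-value is (b + 1)/(B + 1).

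- b = 0: 1/1001 = 0.000999
- b = 1: 2/1001 = 0.001998

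**2. Bonferroni threshold, 0.05/m**

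| m | 0.05/m | Exceedances allowed |
|---|---|---|
| 20 | 0.0025 | 0 or 1 |
| 25 | 0.0020 | 0 or 1 |
| 26 | 0.00192 | 0 only |
| 50 | 0.00100 | 0 only |
| 51 | 0.00098 | none: significance impossible |
| 100 | 0.00050 | none: significance impossible |

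If the observed arrangement is counted among the 1,000, the floor is exactly 0.001 and, with the strict inequality, the limit drops to 49 tests.

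**3. Monte Carlo noise from 26 to 50 tests.** Take a factor whose p-value with unlimited permutations would be 0.0005, half the threshold at m = 50. The chance of zero exceedances is (1 − 0.0005)^1000 = 0.61. It is therefore missed with probability 1 − 0.61 = 0.39, although its true p-value is below the threshold.

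**4. How many tests are plausible?** These counts are assumptions, because the article lists variables but not PERMANOVA factors.

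- Counting the variables under Measurements gives about 49 or 50, depending on how items are split: about 21 clinical and socio-demographic, 10 anthropometric, 10 blood and milk profiles, 4 dietary and 5 from questionnaires. Adding six post-natal factors named in the Introduction (sex, birth order, gestational age, delivery mode, home setting, pets) gives 50 + 6 = 56. So 49 to 56 tests at 12 months sit on or over the limit.
- If the six infant ages are pooled into one family, 9 factors × 6 = 54 crosses it, while 8 × 6 = 48 does not.
- Twenty factors at 12 months only stays clear: the threshold 0.0025 is above 2/1001.

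**5. Permutations required.** The floor lies below the threshold when 1/(B + 1) < 0.05/m, that is, when B + 1 > 20m.

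- m = 51: at least 1,020
- m = 100: at least 2,000
- B = 9,999: floor 0.0001, enough for m up to 499
- B = 99,999: floor 0.00001, enough for m up to 4,999

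The Monte Carlo standard error at p = 0.001, √(0.001 × 0.999/B), is about 0.0010 with B = 1,000 and 0.0003 with B = 9,999.

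**The case against.** The arithmetic is not in dispute; the trigger is. No passage states how many PERMANOVA tests will be run, and defining the family is something an article may leave to an analysis plan that is not shown. The candidate count is soft. Six of the 56 factors come from the Introduction's review of earlier studies, and without them the count is about 50, where significance is still just attainable. Some entries overlap, such as smoking and smoke exposure, or emotional status and the stress and depression scales. The blood and milk assays are multivariate profiles that are nowhere named as single PERMANOVA factors.

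A reader might infer that, followed as written, the plan has zero power for every factor. The documents do not support that, because they fix no m. A reader might also multiply all the factors by six ages, but objective 3 concerns 12 months only, so pooling over ages is one possible reading and not the stated one. Nor is PERMANOVA shown to be the main test for objective 3: the same section assigns the association of predictors with gut microbiota to the generalized linear model with confounder adjustment, and that model has no such floor.

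These points stand, and they make the finding conditional. They do not remove it. The article fixes the permutation count while tying the level to however many comparisons are made, so an undefined family does not protect the plan. Software that reports b/B can return p = 0 and hide the floor, but that is not a valid permutation p-value.

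**Conclusion.** The concern holds as a condition. With more than 50 PERMANOVA tests in the Bonferroni family, no factor can reach significance, whatever its effect. With 26 to 50 tests, only zero exceedances will do, and a factor with a true p-value of 0.0005 is lost about 39% of the time. With about 20 tests at 12 months the floor does not bind.

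This rests on the (b + 1)/(B + 1) p-value and on Bonferroni covering PERMANOVA, as the unqualified wording implies. That the family reaches 26 or 51 tests is plausible from the variables listed, but it is an inference. The generalized linear model for objective 3 is untouched. This is a stated number that clashes with a stated rule over a realistic range of test counts. It is worth correcting because the correction is almost free; it is not a demonstrated failure of the study.

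**What to change.** In the Statistical analysis section, replace the 1,000 permutations with at least 9,999, or with 99,999 if the family may be larger than 499 tests. Add that the number of permutations plus one will be well above 20 times the number of PERMANOVA tests in the family, and say which tests form that family.

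Bonferroni can stay. Benjamini–Hochberg control of the false discovery rate is an option, but this defect does not require it.

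The cost is a change of wording and some computing time. No data, sample or participant burden is involved.

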## Introduction

Gut microbiota plays a critical role in children's developmental pathways, especially in the first 1,000 days of life, due to the interplay between the establishment of the risks for diseases over infants' life course and infant health (1–3). Infant gut microbiota develops after birth, but the initial bacterial colonization occurs as early as when the fetus is still in the lower uterus (1). However, microbial diversity and colonization patterns vary at different time points and among infants (1, 4). More than 95% of the microbiota composition in the infant's intestinal area could be categorized into four major phyla: Firmicutes, Bacteroidetes, Actinobacteria, and Protecteobacteria (1). Two major transitions take place in the gut microbiota during infancy. The first transition characterizes the dominance of Bifidobacterium right after birth and during lactation, followed by the dominance of Bacteroidetes and Firmicutes during the weaning period, the introduction of solids foods, and continued breastfeeding practices, marking the second transition (4, 5).

Recently, increasing evidence have shown the impacts of pre-natal maternal factors on infant gut microbiota through the transmission of metabolic diseases passed from mother to child. The maternal factors are primarily associated with physical health before and during pregnancy as indicated by high pre-pregnancy body mass index (BMI) (6–8), unhealthy weight gain (6, 8), maternal exposure to medications (7–10), and gestational diabetes mellitus (GDM) (7, 8, 11). Furthermore, environmental factors involving maternal diet, including high-fat diet (7, 8, 12), smoking (10, 13), and food insecurity (14) during pregnancy are linked to the changes in infant gut microbiota. The variations in infant gut microbiota due to diet diversity among Malaysian pregnant women of different ethnic groups and the differences between Western and Eastern diets are worth investigating. Additionally, previous studies have shown that breast milk composition (4, 10, 15, 16) and maternal gut microbiota (7, 10) are linked to infant gut microbiota. Nevertheless, the composition of breast milk and gut microbiota of Malaysian women and their effects on infant gut microbiota remains unknown.

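### PERMANOVA, the only named whole-community test of composition, also responds to within-group spread; a dispersion test on the same Bray-Curtis matrix should be reported beside it

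*Protocol article*

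**What the plan says.** The Statistical analysis section names the test and distance, "Permutational multivariate analysis of variance (PERMANOVA) based on Bray–Curtis distances", with 1,000 permutations. It gives the test its role: it "will be used to evaluate which factors are associated with the composition of the microbiota".

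Other analyses stand beside it in the same section:
- an ordination display: "Principal coordinate analysis (PCoA) plots with phylogenetic and non-phylogenetic distances will be plotted";
- one-way ANOVA and Tukey tests on richness, diversity measures, bacterial load and abundances;
- a generalized linear model "to determine the associations between predictors and gut microbiota and the association between gut microbiota and infant health after controlling for confounders".

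On error control, "The significance level for all statistical analyses will be set at *p* < 0.05", and "the Bonferroni correction will be applied to counteract the effect of multiple testing and avoid multiple spurious positives". The number of comparisons is not given.

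No test of multivariate dispersion is named. The article gives no group sizes for any exposure and no figure for spread within exposure groups.

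**The concern.** The third specific objective in the Introduction is to find which socio-demographic, prenatal and postnatal factors are associated with the infant gut microbiota at 12 months. For whole-community composition, the named test is PERMANOVA.

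Many of the factors are observed exposures: antibiotics, probiotics, smoking and alcohol in the Clinical data section, and gestational diabetes and delivery mode in the Introduction. Such groups are unlikely to be of equal size. The Introduction also says that "microbial diversity and colonization patterns vary at different time points and among infants", so variability between infants is an expected feature of these data.

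If one exposure group is more heterogeneous than the other, PERMANOVA can be significant although the typical composition is the same. Without a dispersion result, a reader cannot tell a factor that shifts the community from one that makes infants less alike. The two call for different interpretations.

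**Working it through.** **Inputs.** From the article: PERMANOVA, Bray-Curtis, 1,000 permutations, 5% level (Statistical analysis); 225 pairs and 29.0% attrition (Participant selection). The article states no PERMANOVA error rate that could be reproduced. Completers: 225 × (1 − 0.29) = 159.75, about 160. Group splits and spread ratios are assumptions.

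**Statistic.** For groups A and B with n_A + n_B = N:

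SSW = (1/n_A) Σ d²ᵢⱼ (pairs in A) + (1/n_B) Σ d²ᵢⱼ (pairs in B); SSA = SST − SSW; pseudo-F = SSA / [SSW/(N − 2)].

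With two groups and SST fixed, p = (1 + number of permutations with SSW no larger than observed) / (P + 1).

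**Why direction matters (Euclidean case, equal centroids).** Per dimension,

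E[SSA] = (n_B σ_A² + n_A σ_B²)/N

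E[MSW] = [(n_A − 1)σ_A² + (n_B − 1)σ_B²]/(N − 2)

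For 32 v 128 and an SD ratio of 1.5:
- Smaller group more variable: E[SSA] = 0.8 × 2.25 + 0.2 × 1 = 2.00; E[MSW] = (31 × 2.25 + 127)/158 = 1.245; ratio 1.61.
- Larger group more variable: E[SSA] = 0.8 × 1 + 0.2 × 2.25 = 1.25; E[MSW] = (31 + 127 × 2.25)/158 = 2.005; ratio 0.62.
- 80 v 80: E[SSA] = 0.5 × 2.25 + 0.5 × 1 = 1.625; E[MSW] = (79 × 2.25 + 79)/158 = 1.625; ratio 1.00.

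The permutation reference lies near 1, so the first case rejects too often and the second too rarely.

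**Simulation A.** Gaussian, 50 dimensions, Euclidean distance, identical centroids, 999 permutations, 500 replicates. Rejection at 5%, for SD ratio 1.5 / 2:

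| Split | Equal spread | Smaller group more variable | Larger group more variable |
|---|---|---|---|
| 80:80 | 3.2% | 5.6% / 4.6% (first group more variable) | 5.4% / 4.8% (second group more variable) |
| 48:112 | 5.2% | 48.2% / 80.0% | 0% / 0% |
| 32:128 | 4.6% | 78.6% / 96.2% | 0% / 0% |
| 16:144 | 3.0% | 92.2% / 100% | 0% / 0% |

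**Simulation B.** Bray-Curtis, the planned distance. Dirichlet compositions on 60 taxa, same mean composition in both groups, concentration 30 v 20 / 30 v 15 (lower means more variable), 1,000 permutations, 500 replicates:

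| Split | Equal (30 v 30) | Smaller group more variable | Larger group more variable |
|---|---|---|---|
| 80:80 | 5.0% | 35.6% / 98.4% (first group more variable) | 38.2% / 92.6% (second group more variable) |
| 48:112 | 5.2% | 29.6% / 96.6% | 10.0% / 80.6% |
| 32:128 | 5.8% | 36.2% / 77.6% | 5.4% / 60.6% |
| 16:144 | 5.0% | 29.6% / 71.8% | 1.2% / 4.4% |

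The Monte Carlo standard error at 5% is √(0.05 × 0.95/500), about 1 point. In B the shared mean composition was redrawn for each cell, so small differences between cells mean little.

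A second Bray-Curtis setting (50 equally abundant taxa, uniform noise, ratio 1.5 / 2) was more extreme: 100% at 80:80 and 48:112 in either direction. At 16:144 it gave 99.8% / 100% with the smaller group more variable and 3.0% / 31.4% with the larger. Equal spread gave 3.8% to 5.4%.

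**Reading.** With equal spread the test holds its level at every split. Under Bray-Curtis, unequal concentration is detected even with balanced groups, because equal mean proportions do not give equal centroids in Bray-Curtis space. Imbalance then governs how strongly the direction of the spread difference matters.

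**Would a robust test settle it?** A Welch-type W*d test was tried under Bray-Curtis with 160 infants. At 24 v 136 it cut rejection from 56% to 23% with the smaller group more variable, but raised it from 10% to 36% with the larger. At 80 v 80 it matched PERMANOVA (62% to 64%).

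**The case against.** The strongest reply is that PERMANOVA on Bray-Curtis is standard and that a condensed article may leave a companion dispersion check to a fuller plan. That limits the weight of the point. It does not remove it, because the article itself fixes the test and what it is to show.

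A second reply is that the article asks only about association. A factor that makes communities more variable is associated with composition, and under exchangeability the permutation test keeps its level. That also stands: the stated 5% is not shown to be wrong for the hypothesis of no association. But the same spread difference is found often or rarely according to which group is smaller, so the result is hard to read without a dispersion test.

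Four stronger readings are tempting and not supported:
- *PERMANOVA alone decides.* The article does not say so. It also plans a confounder-adjusted GLM, ordination plots and tests on abundances. None of these, nor Bonferroni, formally separates spread from location.
- *Unequal groups cause the problem.* Under Bray-Curtis, balanced groups reject too, and with equal spread unequal groups do not.
- *Spurious associations will be reported.* That needs unequal spread between exposure groups, on which the article gives no figure. Its remark on variation among infants does not supply one. The rates above are also at an unadjusted 5%, before the planned Bonferroni correction.
- *True shifts will be missed when the larger group is more variable.* A Bray-Curtis check with a modest true shift did not confirm this: power was 40% to 94%, against 37% to 78% with equal spread.

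**Conclusion.** The point holds in a limited form. PERMANOVA is the only whole-community test named, and a significant result can reflect variability rather than a shift in composition. Under the assumed spread differences, with 160 infants and an unadjusted 5% level, rejection with the smaller group more variable ran from about 30% to 97% under Bray-Curtis with Dirichlet data (splits 48:112 to 16:144) and from 48% to 100% under Euclidean distance. With the larger group more variable it was 1% to 81% and 0% respectively. With equal spread it stayed at about 3% to 6%.

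These figures show that the sensitivity exists and that its direction matters. They do not predict this cohort's error rate, since the splits and spread ratios are assumed. The point is a cheap improvement.

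**What to change.** Add to the PERMANOVA sentence in the Statistical analysis section:

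> For each categorical factor, a permutation test of homogeneity of multivariate dispersion (distance to group centroid, same Bray-Curtis matrix) will be reported beside the PERMANOVA result. Where dispersion differs, the factor will be described as showing a difference in composition and/or variability, not a shift in composition.

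A Welch-type W*d test may be added as a sensitivity analysis to lessen the effect of unequal group sizes. It should not be used as proof of a location shift, since under Bray-Curtis it removes the sensitivity only in part and can increase rejection when the larger group is the more variable.

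The cost is a few lines of code per factor on a distance matrix that is computed anyway, with no change to data collection. Some factors may lose an unqualified composition label.
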